### Statistical analysis and sample size

Descriptive statistics within each randomised group will be presented for baseline values. These will include counts and percentages for binary and categorical variables, and means and standard deviations, or medians with lower and upper quartiles, for continuous variables, along with minimum and maximum values and counts of missing values. There will be no tests of statistical significance nor confidence intervals for differences between randomised groups on any baseline variable. Data distributions and all model assumptions will be checked for all analyses. If model assumptions are not met, data will either be transformed or analysed using a non-parametric test, as appropriate.

The sample size was calculated on the basis of change in psychotic experiences, since there will be a much larger standardised mean difference for sleep than psychotic-like experiences. Based on the standard deviations observed from previous studies for the SCI (SD = 2.5) and the GPTS (SD = 10.4) [32, 52], a total sample size of 2,614 (1,307 per group) will provide 90 % power to detect a small effect size with a standardised mean difference of 0.15 in psychotic-like experiences (primary outcome), whilst accounting for a high level of expected attrition (40 %).

After randomisation, participants will be analysed according to their allocated treatment group, irrespective of what treatment they actually receive. We will endeavour to obtain full follow-up data on every participant to allow full intention-to-treat analysis but we will inevitably experience the problem of missing data due to withdrawal, loss to follow up, or non-response questionnaire items. Data analysis will be performed using a mixed-effect model for repeated measures. The model will include treatment group, time, treatment-by-time interaction, and baseline covariates. An unstructured correlation matrix will be used to model the within-subject error correlation structure. An appropriate contrast will be specified to test for treatment efficacy between randomised groups for the primary outcome. We will also perform various sensitivity analyses using imputation methods to test whether the results are robust enough to allow for different assumptions about the missing data. The results from the trial will be prepared as comparative summary statistics (difference in response rate or means) with 95 % confidence intervals. All the tests will be done at a 5 % two-sided significance level. The study results will be reported in accordance with the Consolidated Standards of Reporting Trials (CONSORT) 2010 statements [53, 54] and Standard Protocol Item: Recommendations for Interventional Trials (SPIRIT) [55, 56] guidelines.

We will use modern causal inference methods for mediational analyses [57, 58]. This involves using parametric regression models to test for mediation of the digital CBT intervention on psychotic-like experiences through insomnia. Analyses will adjust for baseline measures of the mediator, outcomes, and putative measured confounders. We will include repeated measurement of mediators and outcomes to account for classical measurement error and baseline confounding, and instrumental variable methods (baseline covariate by randomization interactions as potential instruments) to investigate the sensitivity of the estimates to these problems and that of unmeasured confounding [57]. A full, detailed analysis plan, including plans for any interim analysis, subgroup analysis, and sensitivity analysis of the primary outcomes, will be prepared and finalised before the analysis.

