### Participants

We will recruit 2,614 students from UK universities. The inclusion criteria are: those with a positive screen for probable insomnia disorder, as indicated by a score of 16 or lower on the Sleep Condition Indicator (SCI) [34]; and being aged 18 or older. There are no exclusion criteria; we will not omit participants who report no signs of psychotic-like experiences because the dimensional measures of paranoia and hallucinations will be endorsed to some extent by a majority of participants, while we are also interested in other mental health outcomes that will be relevant to all participants (for example psychological wellbeing). Universities across the UK will be approached to take part. At each university, participants will be recruited via email circulars, which will provide a link to the web-based screening. Therefore many thousands of students at each university taking part will receive an invite to take part in screening for the study. Participants will not be recruited via health settings.

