### Randomisation and allocation concealment

This study will use simple randomisation with an allocation ratio of 1:1, as recommended for large clinical trials [35]. It will be carried out by the automated online system, hence the research team will be unable to influence randomisation, and have no access to future allocations.

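### With 40% attrition, 2,614 participants give about 84% power for a standardised difference of 0.15, not the stated 90%; the figure fits multiplying by 1.4 instead of dividing by 0.6

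*Protocol article*

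**What the plan says.** The protocol article, under Statistical analysis and sample size, sizes the trial on psychotic-like experiences, because the effect on sleep is expected to be much larger. It claims that "a total sample size of 2,614 (1,307 per group) will provide" what the trial needs. The target it names is "90 % power to detect a small effect size with a standardised mean difference of 0.15". The claim is made "whilst accounting for a high level of expected attrition", which the section puts at 40%. The same section fixes the significance level: "All the tests will be done at a 5 % two-sided significance level". Randomisation and allocation concealment specifies "simple randomisation with an allocation ratio of 1:1". Participants repeats the target: "We will recruit 2,614 students from UK universities".

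The paragraph gives standard deviations for the SCI (2.5) and the GPTS (10.4). It does not show the attrition step, and it names no baseline–outcome correlation or other reduction in variance.

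**The concern.** A loss of 40% leaves 60% of those randomised, so the evaluable number has to be divided by 0.6. The printed per-group figure is instead almost exactly the evaluable number multiplied by 1.4. The two operations differ considerably at this level of attrition: dividing by 0.6 multiplies by 1.667.

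This calculation is the stated justification for the size of the trial, and it concerns the harder of the two primary targets. The article describes 40% as the expected attrition, so the power at 40% is the planned operating point and not a worst case. If the true figure is nearer 84%, readers would judge a null result on paranoia or hallucinations against a sensitivity that the stated calculation does not support.

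**Working it through.** **Inputs, all from the protocol article**

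- Standardised mean difference 0.15, power 90%, attrition 40%, 1,307 per group (Statistical analysis and sample size)
- Two-sided 5% (same section)
- 1:1 allocation (Randomisation and allocation concealment)

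The effect is given in standard-deviation units, so the GPTS standard deviation cancels. For scale, 0.15 × 10.4 = 1.56 GPTS points.

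**Step 1. Evaluable number per group**

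n = 2(z₀.₉₇₅ + z₀.₉₀)² / d² = 2(1.960 + 1.2816)² / 0.15² = 933.99, so 934 (935 with the t distribution).

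**Step 2. Reproducing the printed figure**

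- 933.99 × 1.4 = 1,307.6 per group. Truncated, this is the printed 1,307, or 2,614 in total. Rounded up it would be 1,308 and 2,616.
- 934 / 0.6 = 1,556.7, so 1,557 per group or 3,114 in total.

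The printed total is 3,114 − 2,614 = 500 below what the stated assumptions require.

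**Step 3. What 2,614 delivers at 40% attrition**

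- Completers per group: 1,307 × 0.6 = 784.
- Power = Φ(0.15 × √(784/2) − 1.960) = Φ(2.970 − 1.960) = 84.4% (84.3% with the t distribution).
- Difference detectable with 90% power: 3.2416 × √(2/784) = 0.164, or about 1.70 GPTS points.
- Attrition at which 90% is still reached: 1 − 934/1,307 = 28.5%.

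**Step 4. Other routes to the printed number**

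| Route | Result | Does it support the text? |
|---|---|---|
| One-sided 5%, divided by 0.6 | 1,270 per group; 90.7% power with 784 | No: contradicts the stated two-sided level and does not give 1,307 |
| 80% power, two-sided, divided by 0.6 | 1,164 per group | No: 90% is claimed |
| 85% power, two-sided, divided by 0.6 | 1,332 per group | No: 90% is claimed |
| Baseline adjustment with r = 0.40, divided by 0.6 | about 1,308 per group | Only with a correlation that the calculation does not state |

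The last route lands on the same number because 1 − 0.40² = 0.84 = 1.4 × 0.6.

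**Step 5. Power with 784 per group if baseline adjustment is credited**

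The effect becomes 0.15/√(1 − r²), taking 0.15 as standardised by the raw-score standard deviation:

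| Assumed r | Power |
|---|---|
| 0 | 84.4% |
| 0.2 | 85.8% |
| 0.3 | 87.6% |
| 0.4 | 90.0% |
| 0.5 | 92.9% |
| 0.6 | 96.0% |

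**The case against.** The strongest reply is that 84% describes an unadjusted comparison of completers, whereas the article plans a mixed model for repeated measures with baseline covariates. The paragraph also speaks of change in psychotic experiences. Under Outcome measures the article reports a test–retest correlation of 0.81 for the GPTS persecutory sub-scale, and a baseline-to-week-10 correlation of only 0.40 would restore 90%. Participants who miss week 10 may still contribute through week 3 or week 22. The multiplication by 1.4 is nowhere written down; it is inferred from a close match, and r = 0.40 with correct division fits about as well.

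Much of this is fair. The cause is an inference, and the power achieved by the planned model may well exceed 84%. But the power statement does not rest on any of it:

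- The calculation lists standard deviations, an effect size and an attrition rate, and no correlation.
- The 0.81 is quoted as a psychometric property, without a retest interval and without any link to the sample size. The correlation over 10 weeks in this population could be lower.
- Reading the outcome as a change score does not rescue the figure. If 0.15 is standardised by the raw-score standard deviation, the effect becomes 0.15/√(2(1 − r)), and power with 784 per group is 71% at r = 0.3 and 84% at r = 0.5.
- No information gain from partial follow-up is quantified.

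It is also true that the error causes no bias and no inflation of type I error, that power stays above 80%, and that the confidence intervals will show the precision actually reached. That limits the consequences but does not make the stated figure correct.

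**Conclusion.** The concern holds. On the article's own inputs, 2,614 randomised with 40% lost leaves 784 per group and gives about 84% power for a standardised difference of 0.15. The claimed 90% applies only to a difference of about 0.164, or to attrition of no more than about 28.5%. The type II error is about 16%, over half as large again as the 10% stated.

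This rests on a two-sample comparison at two-sided 5%, with participants lost to follow-up contributing nothing and no credit for baseline adjustment, which is all that the sample-size paragraph supports. That the factor 1.4 was used is very likely but inferred; the shortfall does not depend on it. If a correlation of about 0.40 or more was in fact assumed, the total could be right, but the assumption would have to be stated.

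**What to change.** Correct the power sentence under Statistical analysis and sample size. The recruitment target can stay as it is. Either of these would do:

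1. Restate the power: *With 2,614 randomised and 40% attrition (784 per group), power is 84% for a standardised mean difference of 0.15, and 90% for 0.164, at two-sided 5%.*
2. Keep 90% and state its condition: attrition of at most 28%, or baseline adjustment with an assumed baseline-to-week-10 correlation of at least 0.40 and a source for that value.

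The cost is one sentence. No participants are added, and no outcome or analysis changes. Under the first option the stated power becomes somewhat less favourable.

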**Methods/Design:**

We will carry out a parallel group, randomised controlled trial of 2,614 students with insomnia in universities across the UK. In the Oxford Access for Students Improving Sleep (OASIS) trial, participants will be randomised to digital CBT for insomnia (in addition to treatment as usual) or treatment as usual. Online assessments will take place at zero, three, 10 (post-treatment), and 22 (follow-up) weeks. Primary outcomes are insomnia and psychotic-like experiences (paranoia or hallucinatory experiences) at 10 weeks. Secondary outcomes are levels of mania, depression, anxiety, nightmares, psychological wellbeing, and the development of mental health disorders. All main analyses will be carried out at the end of the last follow-up assessment and will be based on the intention-to-treat principle. The trial is funded by the Wellcome Trust.

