### Assessment points

Assessments will take place at the key assessment points of 0 (baseline), three (mid-therapy), 10 (end of therapy), and 22 weeks (follow-up). As an ethical consideration, all the control participants will be provided with CBT at 23 weeks, once the 22-week follow-up assessment has been conducted. We will therefore take this opportunity to include a further follow-up at 33 weeks for all trial participants (providing a potential replication of the within group treatment effect).

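### As listed, the primary repeated-measures model gives each baseline covariate one slope for all visits. If the true slope changes over visits and dropout depends on baseline differently by arm, the week-10 and week-22 contrasts can be biased even under missing at random; a baseline-by-time term removes this

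*Protocol article*

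**What the plan says.** All of this is in the protocol article. In Statistical analysis and sample size, the method is named first: "Data analysis will be performed using a mixed-effect model for repeated measures". The fixed effects follow: "The model will include treatment group, time, treatment-by-time interaction, and baseline covariates". The covariance is then set: "An unstructured correlation matrix will be used to model the within-subject error correlation structure". The covariates are not named, and the section does not say whether week 0 enters as a covariate or as one of the responses.

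Assessment points gives visits at weeks 0, 3, 10 and 22. The abstract fixes the primary time point: "Primary outcomes are insomnia and psychotic-like experiences (paranoia or hallucinatory experiences) at 10 weeks". Week 22 carries the secondary hypothesis that effects are maintained.

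The sample size is said to give power for a small effect, a standardised mean difference of 0.15, "whilst accounting for a high level of expected attrition" of 40 %. Blinding states that participants know their allocation. The statistical section also plans imputation-based sensitivity analyses and a check of model assumptions, and it defers further detail to a full analysis plan that is not shown.

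**The concern.** The sentence on model terms crosses time with treatment and with nothing else. Taken literally, a participant's baseline score must predict the week-3, week-10 and week-22 scores with one regression coefficient. If the true coefficient falls over time, the fitted common slope is a compromise that is too steep for the later visits.

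That does no harm while responders in the two arms have the same mean baseline, as randomisation ensures before dropout. It matters once dropout has made responders' baseline differ between arms. The model then corrects for that difference with the wrong slope, and the error goes into the treatment contrast. The unstructured matrix describes the residuals and does not repair the mean model.

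Arm-specific dropout is plausible here. Attrition of 40 % is expected, participants are unblinded, and only one arm is asked to complete six sessions and daily sleep diaries. At stake is the week-10 contrast, where the target effect is only 0.15 SD, and still more the week-22 contrast.

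**Working it through.** **Scale: the plan's own figure.** Per arm, n = 2(1.96 + 1.2816)² / 0.15² = 934. The stated 1,307 per arm equals 934 × 1.4 = 1,307.6; dividing by the retained fraction instead gives 934 / 0.6 = 1,557. That difference is a separate matter and nothing below depends on it. What is needed here is the 0.15 SD target and the 40 % attrition.

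**Mechanism.** Let β_t be the true baseline slope at visit t, β_c the fitted common slope, and Δ_t the CBT-minus-control difference in mean baseline among those still responding (baseline SD 1). Approximately,

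bias_t ≈ −(β_c − β_t) × Δ_t.

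The product is zero if the slopes are equal over visits (β_c = β_t) or if dropout depends on baseline equally in both arms (Δ_t = 0). Both conditions are therefore needed, and the sign depends on which arm loses the more severe participants.

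**Simulation.** Inputs from the article: three post-baseline visits, unstructured covariance, 1:1 allocation, about 40 % lost by the end. Assumed: the baseline slopes, the residual correlations, and the log-odds of dropout per SD of baseline in each arm. The true effect is 0 and the outcome SD is 1. Dropout is monotone at about 18/35/41 % by visit and depends on baseline only, so data are missing at random. Bias was estimated with 400,000 per arm (Monte Carlo error 0.002-0.003).

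| True slope at weeks 3/10/22 | Dropout log-odds per SD, control / CBT | Week-10 bias (SD) | Week-22 bias (SD) |
|---|---|---|---|
| 0.60/0.60/0.60 (flat) | −1 / +1 | −0.001 | −0.002 |
| each falling pattern below | +0.5 / +0.5 | within 0.003 of 0 | within 0.005 of 0 |
| 0.70/0.60/0.50 (mild) | 0 / +0.5 (moderate) | 0.009 | 0.037 |
| | −0.5 / +0.5 (strong) | 0.024 | 0.072 |
| | −1 / +1 (extreme) | 0.041 | 0.127 |
| 0.80/0.60/0.40 (steep) | moderate | 0.028 | 0.079 |
| | strong | 0.059 | 0.152 |
| | extreme | 0.115 | 0.282 |
| 0.50/0.30/0.20 (lower, falling) | moderate | 0.024 | 0.052 |
| | strong | 0.044 | 0.096 |
| | extreme | 0.090 | 0.181 |

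With visit-specific slopes the bias is at most 0.004 SD in every row.

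**Hand check.** Under strong dropout differences Δ is −0.36 at week 10 and −0.45 at week 22. If β_c lies within the range of the true slopes, the mild pattern gives at most (0.70 − 0.60) × 0.36 = 0.036 at week 10 and (0.70 − 0.50) × 0.45 = 0.090 at week 22. The simulated 0.024 and 0.072 fit under these ceilings. For the steep pattern the ceilings are 0.20 × 0.36 = 0.072 and 0.40 × 0.45 = 0.18, against 0.059 and 0.152.

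**Type I error at 1,307 per arm, 600 replicates.** The week-10 standard error is about 0.038.
- Mild decay, moderate/strong: 0.05/0.08 at week 10 and 0.13/0.37 at week 22.
- Steep decay, moderate/strong: 0.13/0.33 at week 10 and 0.37/0.86 at week 22.
- Visit-specific slopes: 0.03-0.06 at week 10 and 0.03-0.07 at week 22.

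The Monte Carlo error of a 5 % rate is √(0.05 × 0.95 / 600) = 0.009, so 0.05 shows no inflation and 0.08 shows a modest one. As a check on the steep, strong case, 0.059 / 0.038 = 1.55 standard errors of bias implies rejection of about 0.34, close to the simulated 0.33.

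**Week 0 as a response.** With week 0 in the response vector and an unstructured matrix, the change-from-baseline contrasts under strong dropout differences are within 0.006 SD of zero, for both the mild and the steep pattern.

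**The case against.** The strongest objection is that one sentence in a condensed article is being read as a final specification. It does not say that covariates enter as main effects only, and a full analysis plan is promised. This stands in part: the common slope is a literal reading, not a confirmed analysis. But the article does list the model's terms and names one time interaction explicitly. Adding the second improves a stated choice; it is not a demand for missing detail.

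The text also leaves open that week 0 is among the responses. If so, the planned unstructured matrix already allows visit-specific slopes for the outcome's own baseline. That stands too, and it is why the point is conditional.

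A reader might infer that arm-specific dropout alone biases the primary result. It does not: with equal slopes over visits there is no bias even under extreme dropout differences. A reader might also take the SCI entry limit of 16 as evidence that the slope decays. Selecting on a predictor leaves a linear regression slope unchanged, so the limit shows nothing of the kind. Nor do the documents support a claim that type I error is inflated at week 10 in general; with mild decay and moderate dropout differences it stays at 0.05.

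The planned assumption checks could expose a changing slope, and the imputation analyses might help. Neither is specified closely enough to guarantee a correction of the primary estimate.

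**Conclusion.** The point holds as a conditional one. The listed terms omit baseline-by-time, and this biases the visit-specific contrasts under missing at random only when the baseline slope changes across visits and dropout depends on baseline differently by arm. For moderate to strong dropout differences the week-10 bias is about 0.01-0.03 SD with mild slope decay, or roughly 7-20 % of the 0.15 SD target (0.01/0.15 to 0.03/0.15). With steeper decay it runs from about 0.03 to 0.09 SD, where values above 0.06 need extreme dropout differences and the single most extreme combination reaches 0.115. Week 22 is hit harder, by roughly two to four times.

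The mechanism is certain. The size is not, since every correlation and dropout slope is an assumption. It also rests on the baseline of the outcome being a covariate and not a response. This is an improvement worth making at almost no cost, not evidence that the planned analysis will mislead.

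**What to change.** In Statistical analysis and sample size, state the model terms as: treatment group, time (categorical), treatment-by-time, baseline covariates, and baseline-by-time, the last at least for the baseline value of the outcome analysed. Equivalently, state that week 0 is part of the response vector, with a common baseline mean in both arms and an unstructured covariance. Apply the choice to the primary and the secondary scales, and carry the same wording into the analysis plan.

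The cost is two extra parameters per covariate (three visit slopes in place of one). In the simulations precision was not lost: the week-10 standard error was essentially unchanged, and at week 22 with steep decay it fell from 0.048 to about 0.045. Conduct, data collection and sample size do not change.

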## Discussion

There is growing interest in the role of sleep in the occurrence of mental health problems. The clinical implication is that improving sleep, using established interventions such as CBT, can lessen other mental health disorders. For example, a recent trial protocol describes a test of CBT to reduce the occurrence of depressive symptoms [59]. Our focus is upon sleep and psychotic experiences. The OASIS study has a strong mechanistic element, aiming to show the causal role of sleep in paranoia and hallucinations, as well as demonstrate the potential wide-ranging clinical benefits of the easily disseminated digital intervention. The study design benefits from being administered online, allowing us to recruit a large sample and limit researcher bias during the conduct of the study. It will, however, recruit a fairly homogenous sample of the population (university students), and this will limit the generalizability of the results. Nonetheless the study will still provide a strong test of the principal hypothesis that insomnia is a contributory causal factor in the occurrence of psychotic-like experiences. The CBT programme makes no reference to psychotic-like experiences and the techniques used are those designed to improve sleep; hence, there will be a clear manipulation of sleep, allowing causal inferences to made about the relationship to psychotic-like experiences.

